# METHODS

## Study parameters/endpoints

### Main study parameter/endpoint

The primary outcome measures are serum sex-hormone levels; estradiol (total, free), estrone, testosterone, sex hormone binding globulin.

### Secondary study parameters/endpoints

The secondary measurements include BMI, weight, waist- and hip-circumference, total body fat, abdominal fat (subcutaneous and visceral), fitness (maximal exercise capacity test by the steep ramp protocol) and blood pressure.

### Other study parameters

The main confounders in this study are undesirable changes in total calorie intake and energy expenditure. From literature, we know that it is hard to regulate these factors strictly. Compensation, either unintentional or intentional, occurs quickly.

To regulate these factors to a maximum, we will monitor in several ways and give clear instructions. Monitoring of dietary intake will be performed by questionnaires and online food diaries. Monitoring of exercise behaviour will be done by questionnaires, moving sensors and heart rate monitors. Furthermore, regular measures of body weight will be performed

## Randomisation, blinding and treatment allocation

Randomisation takes place after the run-in phase. It will be performed by the department of data-management of the Julius Center (UMC Utrecht). We will use block randomisation, with a block size of 5, stratified by centrum and municipality.

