# **STUDY DESIGN**

The SHAPE-2 study is designed as a single blind RCT with three study arms. The outcome assessors will be blinded for treatment assignment as much as possible. After a run-in period of 5 weeks, eligible women (n=250) will be randomised into a diet-induced weight loss group (D), a combined exercise- plus diet-induced weight loss group (E), or a waiting list control group (C). This intervention period will take 10-14 weeks. And will be followed by a weight maintenance period of 2-6 weeks, so that the total study duration is 21 weeks.

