## Exclusion criteria

- Presently using sex-hormones

- Maintenance use of corticosteroids

- Suffering breast cancer (or in medical history).

- Suffering other types of cancer now or in the past 5 years, except for non-melanoma skin cancers

- Suffering diabetes mellitus (type 1 and 2) or other endocrine related diseases

- Smoking

- Alcohol or drug abuse

- Any disorder that might impede participation in the exercise programme

- Following, or the intention to follow, a structured weight loss programme elsewhere

- In the investigator’s opinion, subject lacks the ability or motivation to fulfil the study programme completely and/or successfully in either one of the three arms

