## Sample size calculation

Sample size calculations are based on the effect of the interventions on serum estradiol levels. The following comparisons will be made:

1) diet-induced weight loss versus combined exercise- plus diet-induced weight loss

2) diet-induced weight loss versus control

3) combined exercise- plus diet-induced weight loss versus control

The following assumptions are based on the results of the SHAPE study in women with a BMI≥25, the DIANA trial46 and the studies of McTiernan13 and Friedenreich 15:

- Mean log-transformed serum estradiol levels: 2.28 pg/ml
- Log-transformed SD: 0.44 pg/ml
- Change in diet group: -12%; pg/ml
- Change in exercise-weight loss group: -20%: pg/ml
- Power: minimally 80%
- Level of significance: 0.05 for comparison 1 and 0.025 for comparisons 2 and 3 (taking into account multiple testing).
- Drop-out: 5% in all groups
- Non-compliance/contamination: 15%

First, we calculated the sample size for the first comparison, i.e. diet-induced weight loss (n=85) versus exercise-induced weight loss (n=85), since the difference in estradiol levels between these groups is expected to be the smallest (8%). Furthermore, we think a difference of 8% will be of clinical relevance. Based on the estimated sample sizes, we calculated the number of subjects needed in the control group (n=36). The sample size of the control group can be much smaller, since the expected difference with the interventions groups is large (12% and 20%, respectively).

The sample size calculations resulted in the following estimated numbers per group, taking into account drop out and non-compliance:

- - Control group: 45
  - Diet group: 104
  - Combined exercise plus diet group: 104

The accompanying power for the other hormones to demonstrate an 8% difference between the diet and exercise group for is tabulated below:

|  | Diet vs. exercise |
| --- | --- |
| Estrone | 83% |
| Testosterone | 100% |
| SHBG | 96% |

*Abdominal fat measured by MRI*

Based on the study of Ross et al.80 (in their obese study population: mean total visceral fat was 2.3 kg SD 0.8 kg), we calculated that 81 subjects are needed to demonstrate a difference of 0.2 kg visceral fat (Alpha=0.05; Beta=0.20.) between the diet and exercise group.

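### A single, published block size of 5 implies 2:2:1, which does not match the planned 104:104:45, and it leaves up to 24% of allocations foreseeable within a stratum

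*Protocol*

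**What the plan says.** Section 5.2 of the protocol places randomisation after the run-in, gives it to the data-management department of the coordinating centre, and continues: "We will use block randomisation, with a block size of 5, stratified by centrum and municipality". It gives no allocation ratio and no variation in block length.

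Section 4.4 lists the numbers per group after allowing for dropout and non-compliance: "Control group: 45", "Diet group: 104" and "Combined exercise plus diet group: 104". These sum to 253. Section 3 says that "eligible women (n=250) will be randomised", and the Summary also gives two hundred and fifty.

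The trial is called single-blind, and section 3 names only the outcome assessors as blinded, as far as possible. The arms are diet and exercise programmes, so participants, dieticians and physiotherapists know the assignment. Under section 3.4, researchers may also make the telephone calls to controls.

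Two provisions leave room for judgement. Section 4.3 excludes a woman if, in the investigator's opinion, the "subject lacks the ability or motivation to fulfil the study programme completely and/or successfully in either one of the three arms". Section 5.4 lets the investigator withdraw a woman who does not meet the inclusion criteria or does not comply with the intervention, on confirmation or strong suspicion.

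**The concern.** Two things follow from one sentence in section 5.2.

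First, the randomisation as specified does not produce the sample sizes that the power calculation relies on. It takes women from the comparison with the smallest expected difference (diet versus exercise plus diet) and gives them to the control arm, which section 4.4 deliberately kept small.

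Secondly, a short block of known length lets someone who sees the assignments work out what remains in the block. If that knowledge affects whether or when a woman is randomised, the groups may differ in motivation or expected adherence. Intention-to-treat analysis does not remove a bias that enters before allocation.

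**Working it through.** **Inputs.** Section 4.4: log mean 2.28; log SD 0.44; changes of -12% and -20%, so differences of 8% (diet versus exercise plus diet), 12% and 20% (each versus control); alpha 0.05 for the first comparison and 0.025 for the other two; power at least 80%; dropout 5%; non-compliance 15%; 85, 85 and 36 before inflation. Section 5.2: block of 5. Assumptions: two-sided tests (sidedness is not stated), and the difference read as a percentage of the log mean.

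**The plan's own arm sizes.** Retained fraction = 0.95 × 0.85 = 0.8075.
- Control: 36 / 0.8075 = 44.6, so 45, as stated.
- Active arms: 85 / 0.8075 = 105.3, and 84 / 0.8075 = 104.0. The stated 104 is reproduced to within two women.
- Control n of 36 against 85: difference 0.12 × 2.28 = 0.2736, alpha 0.025, power 81.2%. This fits the plan.

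**Ratio.** 104 / 45 = 2.31. The splits of 5 with equal active arms and a non-empty control arm are 2:2:1 and 1:1:3, and only 2:2:1 has the smaller control arm.
- 250 women: 250 / 5 = 50 blocks, giving 100:100:50.
- 253 women: 253 / 5 = 50.6, giving about 101:101:51.

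Unfilled last blocks do not close the gap. In a simulation of 253 women spread at random over 2 to 30 strata (4,000 runs each), exactly 104:104:45 arose in at most 0.1% of runs. The number of municipalities is not given, hence the range.

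**Power.** Normal approximation: power = Φ(δ / [σ√(1/n₁ + 1/n₂)] − z), with n multiplied by 0.8075.

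Diet versus exercise plus diet: δ = 0.08 × 2.28 = 0.1824, δ/σ = 0.4145, z = 1.960.
- 104 per arm, 83.98 retained: 0.4145 × √(83.98/2) = 2.686; Φ(0.726) = 76.6%.
- 100 per arm, 80.75 retained: 0.4145 × √(80.75/2) = 2.634; Φ(0.674) = 75.0%.

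Diet versus control: δ/σ = 0.2736 / 0.44 = 0.6218, z = 2.241.
- 83.98 against 36.34: 3.132; Φ(0.890) = 81.3%.
- 80.75 against 40.38: 3.226; Φ(0.985) = 83.8%.

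| Arms | Diet vs exercise plus diet | Diet vs control | Exercise plus diet vs control |
|---|---|---|---|
| 104:104:45 | 76.6% | 81.3% | above 99% |
| 100:100:50 | 75.0% | 83.8% | above 99% |
| 101:101:51 | 75.4% | 84.4% | above 99% |

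**Predictability.** Two diet, two exercise plus diet and one control can be ordered in 5! / (2! 2! 1!) = 30 ways.
- An allocation is certain when all remaining places belong to one arm. That always holds at position 5. At position 4 it needs the last two places to be the same arm: 2 of the 10 possible pairs, or 0.20. Share certain = (1 + 0.20) / 5 = 24%.
- Control is ruled out once it has been used: (0 + 0.2 + 0.4 + 0.6 + 0.8) / 5 = 40%.
- Best guess by position: 0.40, 0.50, 0.533, 0.60, 1.00; mean 60.7%. Without knowledge of earlier allocations it is 40%.

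Unfilled last blocks lower the certain share for 253 women: 23.6% with 2 strata, 23.1% with 5, 22.2% with 10, 20.5% with 20 and 18.8% with 30.

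**The case against.** **The ratio mismatch is small.** Section 4.4 calls its numbers estimates. At 253 women, 2:2:1 takes about three from each active arm, and diet versus control gains power. This stands. A reader might infer that the block size pulls the main comparison below its 80% target. The documents do not support that: with 8% of 2.28 and SD 0.44, power is already 76.6% at 104 per arm, so most of the shortfall precedes the ratio and is a separate sample-size question.

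**The 24% is a ceiling.** It requires knowledge of the block size and of every earlier allocation, in order, within one stratum. It also assumes women are randomised one at a time, which section 5.2 does not say. The group diet sessions at fixed study weeks suggest that women may start in cohorts, and allocating in batches would weaken sequential guessing. This stands, and the figure should be read as an upper limit.

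**The timing limits misuse.** Under section 8.2, consent and eligibility screening come first, followed by the dietician's intake and five weeks of run-in. A recruiter at screening cannot know which block position a woman will take. The motivation criterion is judged against all three arms, not an expected one. A reader might infer that recruiters can screen women in or out against a known next assignment. The documents do not support that. What remains is the end of run-in: section 5.4 allows withdrawal on suspicion, the randomisation date could be shifted, and nothing says that eligibility is locked before the assignment is released.

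**Allocation is central.** This keeps the list hidden, but not the assignments already made, which staff see. It does not prevent inference from a known block length.

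**Conclusion.** The point holds on two counts, neither fatal.

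1. **Internal contradiction.** A block of 5 implies 2:2:1 and cannot deliver 104:104:45, and 250 conflicts with 253. The effect is about 3 to 4 fewer women per active arm and 5 to 6 more controls. It costs the diet versus exercise plus diet comparison 1 to 2 percentage points of power.
2. **Avoidable weakness in concealment.** Up to 24% of allocations are certain to a fully informed observer (about 19-24% over 2 to 30 strata), and the best guess is right 61% of the time against 40%. This is the more important half, but it is exposure, not evidence of bias.

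This rests on 2:2:1 being inferred, two-sided tests, the effect taken as a percentage of the log mean, and one-at-a-time randomisation. The power levels depend heavily on the effect scale, but the cost of the ratio does not. Taking ln(0.88/0.80) = 0.0953 as the difference gives Φ(0.2166 × √41.99 − 1.960) = 28.9% against Φ(0.2166 × √40.375 − 1.960) = 28.0%, again about one point.

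**What to change.** - In section 5.2, state the ratio 2:2:1. Have the data-management department use randomly mixed blocks of 5 and 10, with the lengths kept out of the protocol and from recruiting staff.
- Require final eligibility after the run-in to be confirmed in the database before the allocation is released.
- Bring the Summary, section 3 and section 4.4 to one total and to the arm sizes that 2:2:1 gives (100:100:50 for 250), and restate the power for all three comparisons. If 104 per active arm is to be kept, 2:2:1 needs 104 / 2 × 5 = 260 women with 52 controls.

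Mixing the blocks is worthwhile. In a simulation with strata of 125 and an observer who knows the lengths are 5 or 10, certain allocations fall from 24% to about 6.6%, and best-guess accuracy from 61% to 57%.

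The cost is a new randomisation list and a few sentences. Balance within small strata becomes slightly looser, and at 250 women the stated diet versus exercise plus diet power is slightly lower.

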## Study procedures/data collection

**Physical examination**

*Anthropometry*

- - Body weight and height

Body weight and height (to the nearest 0.5 kg and 0.5 cm respectively) will be measured while the subjects wearing light clothes and without shoes using an analogue balance (SECA) and wall-mounted tape measure.

- - Body fat distribution, i.e waist and hip circumference

Waist circumference (to the nearest 0.1 cm) is measured standing at the midway between lower ribs and iliac crest. Hip circumference (to the nearest 0.1 cm) is measured standing over the buttocks. All measurements were taken in duplicate and averaged.

- - Total body fat and body fat percentage

Total body fat and body fat percentage will be determined by using a total body DEXA scan (Lunar, Prodigy ™). A total body scan analyses body composition according to a three-compartment model: fat mass, lean tissue, and bone mineral content. The standard soft tissue analysis was performed using software supplied by the manufacturer. Total body fat will be estimated for each subject in kilograms. The DEXA scan will only be used for measurement of body composition (total body fat and muscle mass). The scan will not be diagnostically screened for pathology.

- - Intra-abdominal fat

Intra-abdominal fat will de measured by an abdominal MRI scan (Philips MR Tesla 1.5 system), using the three-point IDEAL method (described by Dixon)81. Visceral adipose tissue (VAT) and subcutaneous adipose tissue (SAT) will be measured by segmentation with the help of semi-automatic software. **The MRI-scan will only be used for VAT and SAT measurements for scientific research purposes and not be screened for pathology by radiologists.**

*Blood pressure*

- - Blood pressure will be measured with an automatically tonometer after participants have been sitting quietly for at least five minutes.

#### *Fitness*

- - Fitness will be defined by peak heart rate, VO2 max and maximal workload. VO2 max will be estimated by a maximal cycle test with the help of a (standard) ramp protocol as follows:
    - 2 minutes of rest while sitting on the ergometer for measuring resting heart rate and ECG.
    - 3 minutes of cycling without workload (warming-up)
    - From minute 6 till the peak heart rate has achieved the workload will be increased every minute by either 12.5 Watt/min, 15 Watt/min, 17.5 Watt/min or 20 Watt/min, depending on the predicted maximum Watt per subject.

Predicted maximum Watt (standard formula) =

((20.4 (cm) – 8.74*(age) – 288 – 1909) x 0.1635. Divided by 10 gives a number which will be rounded off to the nearest Watt/min.

The maximal exercise capacity test will be performed in a clinical setting. During the whole test ECG will be performed. There is safety and reanimation equipment and an alarm button available within hand reach of the supervisors. There are always two supervisors performing one test, both are trained on supervising maximal capacity tests. At least one is trained in reanimation, ECG reading (especially focusing on ischemic signs) and recognizing of stop criteria.

- *Physical activity*
  - Physical activity is measured by the ActiGraph, an activity monitor. The ActiGraph is non-invasive. It will be worn twice by all participants in the run-in and maintenance phase during 7 consecutive days.

**Blood samples**

- - Blood samples will be drawn in order to determine serum concentrations of estradiol (total, free), estrone, testosterone and sex hormone binding globulin (SHBG). Blood samples will be centrifuged and stored at -80C within 4 hours. All samples from an individual subject will be analysed in the same batch since the batch-to-batch variation can be higher than any woman's likely change in hormones over the year82.Serum estrogens, testosterone and SHBG will be determined by use of commercially available double-antibody radioimmunoassay kits (Roche Cobas: SHBG-03052001, testosterone-05200067190) and LDN: estradiol US ELISA E-1900, estron FR E-2300). The laboratory ”Stichting Huisartsenlaboratorium Oost” in Velp ([www.labsho.nl](http://www.labsho.nl/)) will perform all assays.

**Questionnaires/interviews**

#### *General*

- - A self-constructed questionnaire (general questionnaire) will be used to determine socio-demographic variables, smoking history, medical history and reproductive factors

#### *Physical activity*

- - Current level of physical activity is measured via the Short-Questionnaire to Assess Health-enhancing physical activity (SQUASH).83 This questionnaire will be filled in once by all participants.
  - Life-time physical activity will be measured via a questionnaire designed by Friedenreich et al. This questionnaire will be filled in once by all participants.84
  - To be able to measure changes in physical activity during the study the PASE-questionnaire is used. (Physical Activity Scale for the Elderly).85 This questionnaire will be filled in twice by all participants.

#### *Diet*

- - Daily food intake will be assessed by the dietician in a one-hour individual session. The focus will be on (total) calorie intake, macronutrients, fibre and alcohol intake
  - An online food-diary on the Dutch website [www.dieeninzicht.nl](http://www.dieeninzicht.nl/) will be used to monitor dietary intake over 3 consecutive days during the study. This diary includes information on macronutrients, dietary fibre and total amount of calories. This diary will be filled in three times during the study period by all participants.

#### *Medication use*

- - Medication use will be asked during the screening- and measurement visits and registered by use of an electronic database.

**Incidental findings**

Measurements will be reviewed on study outcome parameters only and can not be seen as a medical screening. However, incidental findings can arise in the different measurements, as high blood glucose level or deviations on the exercise ECG, these will always be reported to the subjects.

MRI-scan: MRI scans are not reviewed by a radiologist. N**ew MRI-scans will be monthly screened by the SHAPE-2 researchers. And at the end of the study during the VAT/SAT measurement procedure. In case of clearly visible incidental findings the scans will be reviewed by a radiologist and the subject will be informed.**

## Withdrawal of individual subjects

Subjects can leave the study at any time for any reason if they wish to do so without any consequences. The investigator can decide to withdraw a subject from the study for urgent medical reasons or in case the subject is not compliant to the inclusion criteria or study intervention (confirmed or with high suspicion).

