**Nature and extent of the burden and risks associated with participation, benefit and group relatedness:**

Benefit:

A benefit for the participants is that they will loose weight under supervision of a dietician and physiotherapist in a healthy way. This also applies to the control group since they will be offered an adapted weight loss program at the end of the study.

Burden:

-The weight loss programs are quite time consuming.

- Injuries due to exercise can occur, to minimize the risk the intensity of the exercise program will be gradually inclined during the study and supervised by a physiotherapist.

- Several measurements will be performed. At baseline, questionnaires about general health, medical history, reproductive history, exercise habits will be filled out. All participants will visit the hospital in their region for measurements twice including: history taking, physical examination, DEXA-scan, MRI-scan, maximal exercise capacity test and blood sampling. During the measurements, a haematoma can occur after blood sampling. Incidental findings can arise in the different measurements, which will be reported to participants. During the maximal capacity exercise test (clinically occult) pre-existing heart problems can be exposed. To reduce the risk of complications due to ischemia the participant will be screened for ischemic heart disease by ECG monitoring during the exercise test. Emergency equipment and personnel trained to deliver appropriate emergency care will be available.

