## Analysis

Our primary and secondary endpoints will be changes in sex steroid hormones, body composition and fitness during the study. If sex hormones are non-normally distributed, log transformations will be used for analyses. We will analyse the effects by linear regression analysis. We will compare the effects of the diet group versus the exercise group, the diet versus control, and exercise versus control. The main analysis will be performed according to the intention-to-treat principle, where outcomes for patients are analyzed by assigned treatment, regardless of the level of adherence. As a secondary analysis, adherence will be examined as a potential modifier of the intervention effects.

To explore whether changes in body fat (total, abdominal) mediates intervention effects on sex hormone levels, we examined the change in the measure of association pre- versus post adjustment for changes in body fat (in the linear regression model). If the adjustment attenuates the measure of association, then we consider this to be suggestive of mediation. Furthermore, the main effect of total body fat/ abdominal fat on changes in sex hormone levels will also be evaluated in the linear regression models, adjusting for the intervention assignment. This method is based on a paper of Kraemer et al86 which explains that a mediator must show a change during treatment, must correlate with the treatment assignment, and must have a main or interactive effect on the outcome.

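### Section 5.4 permits withdrawal from the study for non-compliance and does not secure the week-21 outcome, in conflict with the intention-to-treat analysis in 7.2

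*Protocol*

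**What the plan says.** Protocol section 5.4 (Withdrawal of individual subjects) gives two grounds on which the investigator may act. The first is medical: "The investigator can decide to withdraw a subject from the study for urgent medical reasons". The second applies "in case the subject is not compliant to the inclusion criteria or study intervention (confirmed or with high suspicion". Withdrawal on either ground is from the study. The section sets no threshold for non-compliance and is silent on measurements after withdrawal.

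Section 7.2 (Analysis) makes the main analysis intention-to-treat, "where outcomes for patients are analyzed by assigned treatment, regardless of the level of adherence". It adds: "As a secondary analysis, adherence will be examined as a potential modifier of the intervention effects".

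On measurement, the Summary states "All participants will visit the hospital in their region for measurements twice", and Figure 1 places these visits in weeks 5 and 21. Randomisation follows the five-week run-in (section 5.2), so week 21 is the only outcome measurement after it.

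On blinding, section 3 says "The outcome assessors will be blinded for treatment assignment as much as possible". It does not say that the person deciding on withdrawal is blinded.

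Section 4.4 (Sample size calculation) assumes "Drop-out: 5% in all groups" and, as a separate item, 15% non-compliance or contamination.

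**The concern.** An intention-to-treat comparison needs outcomes from women who did not follow the programme. Section 5.4 allows those same women to be taken out of the study, on suspicion alone, by someone who may know their arm. With one post-randomisation measurement, a woman withdrawn before week 21 has no change score unless the visit is kept for her, and nothing in the protocol keeps it. Section 6.3 asks only that reasons for absence be checked.

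Such losses need not be random. In the diet arm, adherence is judged partly by body weight (section 3.2), and weight loss is the expected route to lower hormone levels. What has to be complied with also differs by arm. The exercise arm has four hours of exercise a week plus a diet, tracked through attendance registers, exercise logs and an activity monitor (3.3). The diet arm has a diet and group sessions (3.2). Controls must hold their weight and habits and are monitored by four phone calls (3.4). The contrast at stake is exercise plus diet (E) versus diet (D), on which the trial was sized.

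**Working it through.** **Inputs (section 4.4).** 104 women randomised to each of D and E; drop-out 5%; non-compliance 15%; expected estradiol change -12% in D and -20% in E; 85, 85 and 36 women in D, E and control before inflation.

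**The plan's own inflation.** Dividing by (1 - 0.05)(1 - 0.15) = 0.8075:
- 85 / 0.8075 = 105.3 (stated 104);
- 36 / 0.8075 = 44.6 (stated 45).

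This is close but not exact for the larger arms. The 85 is taken as given, since nothing below depends on how it was derived.

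**Outcomes available per weight-loss arm.**
- Non-compliers stay in follow-up: 104 x 0.95 = 98.8, about 99; missing 5%.
- All assumed non-compliers withdrawn: 104 x 0.95 x 0.85 = 83.98, about 84; missing 1 - 0.8075 = 0.1925, about 19%.
- Difference: up to about 15 further outcomes lost per arm.

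**Effect on the E versus D estimate.** Assumptions that are not in the protocol: non-compliers show no change, compliers show the full stated change, the 15% applies equally to D and E, and the 5% drop-out is unrelated to outcome.

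Full effects on the log scale: D, ln 0.88 = -0.1278; E, ln 0.80 = -0.2231. If a share w of an arm's non-compliers is withdrawn, the mean among those left is the full effect x 0.85 / (1 - 0.15w). With w = 0 the factor is 0.85; with w = 1 it is 1.

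| Non-compliers withdrawn | E reduction | D reduction | Difference | Relative to ITT |
| --- | --- | --- | --- | --- |
| None (ITT) | 0.1897 | 0.1087 | 0.081 | reference |
| Both arms | 0.2231 | 0.1278 | 0.095 | +18% |
| E only | 0.2231 | 0.1087 | 0.114 | +41% |
| D only | 0.1897 | 0.1278 | 0.062 | -24% |

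The difference rises with w in E and falls with w in D, so under these assumptions 0.062 and 0.114 are the extremes and partial use of the discretion falls between them. Equal removal in both arms still shifts the estimate, because it replaces the effect of assignment with the effect among compliers.

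**The case against.** The strongest reply is that 5.4 only permits withdrawal. The investigator may never use it for non-compliance, and 5.4 does not say that week-21 measurements lapse. Other sections lean towards keeping poor adherers: 3.2 and 3.3 answer missed weight-loss targets with more coaching or an adapted diet or programme, 4.4 lists drop-out and non-compliance separately, and 7.2 plans an adherence analysis that needs these women. Consent is signed before the run-in (8.2), so the inclusion-criteria ground can also apply before randomisation, where it does no harm to intention-to-treat. All of this stands. It makes loose drafting more likely than an intended complier analysis. It does not remove the conflict, because non-compliance with the allocated intervention can arise only after randomisation and nothing secures the sample.

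A reader might go further and infer that:
- *the rule does remove outcomes selectively by arm.* The unequal demands make this plausible, but no arm-specific withdrawal rates are given and 4.4 assumes equal drop-out.
- *controls cannot be non-compliant.* Section 3.4 asks them to hold weight and habits.
- *the effect will be overstated by 41%.* That is one corner of the table; another corner understates it by 24%.
- *the inflation shows that non-compliers were meant to be lost.* The arithmetic gives 105.3 against a stated 104, which is too loose to carry that conclusion.

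An analysis plan that is not shown may well set out missing-data methods, but it cannot supply blood samples that were never drawn.

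**Conclusion.** The point holds as a conflict between what 5.4 permits and what 7.2 requires. Where the discretion is used on a randomised woman and week 21 is then omitted, her outcome is lost to both the main and the adherence analysis. The upper limit, if every assumed non-complier is withdrawn, is about 19% missing outcomes instead of 5%. Under the no-effect assumption for non-compliers, the E versus D estimate could move by anything from -24% to +41%, and by +18% with full removal in both arms. These are illustrations, not forecasts: how often the clause would be used and in which arm are unknown, so neither the size nor the direction of the bias can be fixed from the protocol.

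**What to change.** Reconcile 5.4 with 7.2 by adding to 5.4 that non-compliance with the intervention, or an eligibility doubt arising after randomisation, does not by itself end follow-up. The week-21 outcome measurements, at least the blood sample, are then sought from every such woman unless she withdraws consent, and she is analysed in the group to which she was assigned.

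The urgent-medical-reasons clause should stay as it is, and when a programme stops remains for the investigators.

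The cost is one paragraph in 5.4. The week-21 visit is already scheduled for all participants, so no new visit is needed.
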